### (1) Questionnaires on subjective symptoms, functional limitation, and quality of life

- Numeric Rating Scale (NRS) – assessed separately for low back pain and leg pain.
- Oswestry Disability Index (ODI).
- European Quality of Life 5 Dimension (EQ-5D)–5L.
- Roland–Morris Disability Questionnaire (RMDQ).

### (2) Physical examination

- Lumbar range of motion (ROM):  
Flexion, extension, lateral flexion (right and left), rotation (right and left).

### (3) Vital signs

- Sitting blood pressure, pulse rate, and body temperature are measured **after at least 5 minutes in the sitting position without abrupt postural changes.**

### (4) Imaging examination

- No separate imaging assessment is performed at Visit 2; the imaging evaluation at Visit 2 is replaced by the screening radiographs obtained at Visit 1.

---

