## ○ Provision of relevant evidence for clinical practice in Korean medicine

- Chuna imaging diagnosis based on radiological data, together with extraction of imaging biomarkers, can serve as an objective basis for comparing and evaluating the effects of Chuna treatment before and after the intervention. This will enable the accumulation of more rational and objective clinical data for future Chuna-related clinical research.
- The development of biomarkers and diagnostic techniques for rational Chuna diagnosis can be used as foundational research to support future insurance coverage (reimbursement) of Chuna diagnostic procedures.

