#### (2) Determination of malposition based on angular values

- Based on the angles derived by the program, the presence or absence of malposition is determined.

- Using the previously derived threshold values for malposition diagnosis (cut-off angles), segments with angles equal to or exceeding the threshold are classified as having Chuna-defined vertebral malposition (for example, if the flexion angle of L1 is 3°, it is diagnosed as a flexion malposition).
- For rotational malposition of L5, there is no separate segment below L5. Therefore, the value is used only when the left-right distance difference between the sacral ala and the S2 tubercle falls within the normal range specified by the program; otherwise, the value is recorded in the case report form but treated as missing in malposition diagnosis and statistical analysis.
- The reference threshold angles for each lumbar vertebral body are as follows

|                     | Vertebral body |       |       |       |       |
|---------------------|----------------|-------|-------|-------|-------|
|                     | L1             | L2    | L3    | L4    | L5    |
| Flexion(° )         | 0.64           | 3.56  | 5.29  | 8.90  | 8.53  |
| Extension(° )       | 10.46          | 14.95 | 17.61 | 20.76 | 24.47 |
| Lateral bending(° ) | 2.21           | 2.10  | 1.92  | 2.06  | 2.31  |
| Rotation(° )        | 9.49           | 5.19  | 4.59  | 5.87  | 7.13  |

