### 1) Inclusion criteria (Inclusion Criteria)

- ① Age: 19 years or older and 70 years or younger at the time of consent.
  - ② Patients with non-acute low back pain (symptom duration  $\geq 3$  weeks) whose average low back pain intensity during the past week is **Numeric Rating Scale (NRS)  $\geq 4$** .
  - ③ Patients in whom **Chuna spinal malposition** has been confirmed on plain radiographs.
  - ④ Patients who voluntarily agree to participate in the clinical trial and sign the **written informed consent form**.
- 

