#### (4) Imaging examination and assessment of Chuna malposition

① Lumbar spine AP and lateral standing radiographs (L-spine AP & lateral standing view) will be obtained according to the Chiropractic Biophysics standardized

procedures described in **Section 6–1, Radiograph–based Chuna diagnostic method used in the clinical trial.**

② Based on the imaging DICOM files, the presence and type of Chuna spinal malposition will be determined.

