## 3) Treatment visits (Visits 3–10; both groups)

(1) Chuna + usual care group (Group I; Visits 3–10)

- Starting immediately after the baseline visit, participants receive treatment **twice per week for 4 weeks**, for a total of **8 sessions** according to the allocated intervention (usual care + Chuna).

(2) Usual care-only group (Group II; Visits 3–10)

- Starting immediately after the baseline visit, participants receive **usual care only** twice per week for 4 weeks (8 sessions).

(3) Assessments at each treatment visit (both groups)

- Before treatment at each visit, the following items are checked:
  - Occurrence of adverse events since the previous visit.
  - Vital signs: sitting blood pressure, pulse rate, body temperature (measured after at least 5 minutes in the sitting position without abrupt postural changes).

---

**4) Assessment visits** (same for Groups I and II – Visits 2, 10, and 11)

(1) All participants who pass screening will visit the outpatient clinic at baseline, at the end of the treatment period (4 weeks after baseline), and 8 weeks after completion of all treatments (12 weeks after baseline) to undergo the following assessments.

(2) Vital signs

(3) Assessment of subjective symptoms and function

- Primary and secondary efficacy outcomes are assessed using questionnaires on pain intensity and function: NRS, ODI, EQ-5D-5L, and RMDQ.

(4) Physical examination

- Lumbar range of motion (ROM):  
Flexion, extension, lateral flexion (right and left), rotation (right and left).

(5) Imaging evaluation

- Standardized lumbar spine AP and lateral standing radiographs (L-spine AP & lateral standing view) are obtained.
- Based on the acquired images, vertebral-level relative angles (flexion, extension, lateral bending, rotation) and Chuna malposition diagnosis results are derived using a DICOM labeling program and compared across time points.

(Note: No separate imaging assessment is performed at Visit 2; the imaging evaluation at Visit 2 is replaced by the screening radiographs obtained at Visit 1.)

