### 3. Imaging evaluation

- At baseline (screening radiographs), week 4, and week 12, **L-spine AP and lateral standing radiographs** are obtained according to the standardized imaging protocol.
- Using a DICOM labeling program developed by the Korea Institute of Oriental Medicine, the following are calculated for each lumbar vertebral level:

- Relative angles for **flexion, extension, lateral bending, and rotation**,
- **Chuna malposition diagnosis results** based on the predefined cut-off values.
- These imaging parameters are used as secondary or exploratory outcomes to investigate changes in spinal alignment and their association with clinical improvement.

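### The film that must show malposition for entry is also the imaging baseline, so within-group change in malposition can look like correction without a treatment effect; imaging inference should rest on the between-group contrast

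*Protocol*

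**What the plan says.** Inclusion criterion 3 (Protocol, Section 6) admits "Patients in whom Chuna spinal malposition has been confirmed on plain radiographs". Section 5.1.2 (2) defines this by a table of cut-off angles for L1 to L5: "segments with angles equal to or exceeding the threshold are classified as having Chuna-defined vertebral malposition". The decision is made on the Visit 1 film (Section 8, Screening visit, item 4): "Based on the imaging DICOM files, the presence and type of Chuna spinal malposition will be determined".

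No second film is taken before treatment. At the baseline visit, "the imaging evaluation at Visit 2 is replaced by the screening radiographs obtained at Visit 1". Films follow at weeks 4 and 12 in both groups.

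Three places bear on how these films are used:

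- Section 8, Assessment visits, item (5): angles and malposition diagnoses are derived "using a DICOM labeling program and compared across time points".
- Section 14.1, item 3: the parameters are secondary or exploratory outcomes, to "investigate changes in spinal alignment and their association with clinical improvement".
- Section 4.2, on provision of relevant evidence: radiographic diagnosis "can serve as an objective basis for comparing and evaluating the effects of Chuna treatment before and after the intervention".

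By contrast, Section 14.1 says that low back pain NRS change and the exploratory outcomes are compared between the groups. Section 15 lists no imaging analysis by name.

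**The concern.** Selecting people because a measurement passed a threshold, and then using that same measurement as baseline, builds in regression to the mean. Some segments are at or above the cut-off on the screening film partly through measurement error or that day's posture. On the next film such segments lie closer to their usual value, treated or not. At participant level, malposition is present in 100% at baseline by the entry rule, so that proportion can only fall.

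This would be harmless if the imaging conclusion were tied to the control arm. The text points the other way. The named comparison is over time, and the rationale section describes a before-after use. If imaging is handled as a secondary outcome under Section 15 2) b, the methods of the primary outcome apply, and these include within-group paired tests as well as the ANCOVA. A reader following the protocol could report a significant within-arm fall in malposition as alignment correction when none occurred.

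**Working it through.** **The plan's own figure.** The documents state no number for imaging. The only sample size is for NRS, and it reproduces: n = 2 × (1.96 + 0.84)² / 0.96² = 2 × 7.84 / 0.9216 = 17.01, rounded up to 18; 18 / 0.80 = 22.5, rounded up to 23 per group. The 18 is used below as the number of completers per arm.

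**Assumed inputs.** The documents give neither the correlation r between repeat films nor the share p of people beyond a cut-off. Angles are taken as normal, with no treatment effect.

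**Step 1: one flagged segment.** With c the cut-off in SD units, the expected fall is (1 − r) × φ(c) / p. The share losing the diagnosis is L = 1 − P(both films ≥ c) / p.

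| p | r | Fall (SD) | L |
|---|---|---|---|
| 10% | 0.7 | 0.53 | 53% |
| 10% | 0.8 | 0.35 | 44% |
| 10% | 0.9 | 0.18 | 31% |
| 20% | 0.7 | 0.42 | 44% |
| 20% | 0.8 | 0.28 | 35% |
| 20% | 0.9 | 0.14 | 25% |

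So 25-53% of flagged segments lose the label without treatment. Over a wider range (p 5-30%, r 0.70-0.95) it is 15-61%.

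**Step 2: all segments.** Step 1 leaves out segments that newly cross a cut-off on the later film. Take 15 independent angles (5 levels × 3 axes) and entry if any one is beyond its cut-off. The mean count at screening is 15p / [1 − (1 − p)^15]. A person is excluded only if all 15 angles are inside, so the later count is the same expression times 1 − L(1 − p)^14. The relative fall is therefore L(1 − p)^14.

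- p = 10%: 0.9^14 = 0.229. At r = 0.7 the fall is 0.53 × 0.229 = 12%; at r = 0.9 it is 0.31 × 0.229 = 7%.
- p = 20%: 0.8^14 = 0.044. At r = 0.7 the fall is 0.44 × 0.044 = 2%; at r = 0.9 it is 0.25 × 0.044 = 1%.
- If p = 10% is split over the two directions of an axis, L at r = 0.7 is 61% and the fall is 0.61 × 0.229 = 14%.
- If p = 2%, split in the same way, the count goes from 1.15 to 0.52 at r = 0.7, a fall of 0.63 / 1.15 = 55%.

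The number of angles matters. With 10 independent angles the exponent is 9, and the range for p = 10-20% becomes 0.25 × 0.134 = 3% to 0.53 × 0.387 = 21%. The mean absolute angle over all segments moves by 0.05 SD or less in every scenario with p 2-20% and r 0.70-0.95.

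**Step 3: what the tests would do.** Simulated trials with no treatment effect, 15 angles, 18 completers per arm, p 2-10% (split over two directions) and r 0.80-0.95, two-sided 5% level:

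| Test | Worst flagged segment | Malposition count |
|---|---|---|
| Paired t-test within one arm | 31-95% significant | 8-84% significant |
| t-test on change between arms | 4.1-5.3% | 4.3-5.5% |

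The within-arm test rejects too often, by an amount that depends on the assumptions. The between-arm test holds its nominal level throughout.

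**The case against.** The strongest reply is that this is a 1:1 randomised trial. Both arms meet the same entry rule and have films at the same visits, so regression to the mean is equal in expectation and cancels between arms. That stands, and Step 3 bears it out. If imaging is secondary, Section 15 2) b also brings in an ANCOVA with the baseline value as covariate, which is the right contrast. The comparison across time points does not exclude a group comparison, and detailed imaging analysis may properly be left to the SAP. What remains is that the protocol itself names only the comparison over time for imaging, and that the same Section 15 route also brings in the within-group tests.

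Four stronger readings are tempting, but the documents do not support them:

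- That the imaging results will show correction by regression to the mean alone. This holds only for within-group change, and its size rests on figures that the documents do not give. Section 5.1.1 also says that the positioning was chosen for reproducibility.
- That 25-53% describes the fall in malposition overall. It applies to flagged segments only.
- That changes in opposite directions will cancel in mean angles. No section plans a signed mean pooled over directions, and malposition diagnoses are reported alongside the angles.
- That the association of alignment change with clinical improvement will be pooled over arms. Section 14.1 does not say so.

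The before-after sentence in Section 4.2 is rationale, not an analysis rule. It matters only because it shows how the result may be presented.

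**Conclusion.** The point holds in limited form. The screening film both selects participants and serves as imaging baseline, and the one comparison named for imaging is over time. Within-group change in malposition status or in flagged segments is therefore not evidence of correction.

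Under the assumptions above, the artefact is substantial for flagged segments (25-53% losing the diagnosis) and small for the count over all segments (about 1-12%, up to 14% with two-sided tails). It is larger if cut-offs are rarer or if there are effectively fewer independent angles. Normality, independence, r and p are all assumptions, so these figures are illustrative.

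The randomised between-group contrast is unbiased. The NRS primary outcome and the sample size are not affected. This is an inexpensive improvement to secondary or exploratory outcomes, not a flaw in the trial's main comparison.

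**What to change.** In Section 8, Assessment visits, item (5), replace the comparison over time, and add the same text to Section 14.1, item 3:

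> Change from the screening film to weeks 4 and 12 is compared between groups, adjusted for the screening value. Within-group change is descriptive and is not evidence of correction.

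Also state that any association between alignment change and NRS change is estimated with treatment arm taken into account. In Section 4.2, limit the before-after statement to differences between groups.

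The dual use of the screening film can stay, and no particular endpoint, such as change at flagged segments only, needs to be imposed.

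The cost is protocol wording, carried into the SAP if there is one. All films are already planned in both arms, so there are no extra visits or radiographs. The downside is that the trial can make no within-arm claim of alignment correction.

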## 3) Treatment visits (Visits 3–10; both groups)

(1) Chuna + usual care group (Group I; Visits 3–10)

- Starting immediately after the baseline visit, participants receive treatment **twice per week for 4 weeks**, for a total of **8 sessions** according to the allocated intervention (usual care + Chuna).

(2) Usual care-only group (Group II; Visits 3–10)

- Starting immediately after the baseline visit, participants receive **usual care only** twice per week for 4 weeks (8 sessions).

(3) Assessments at each treatment visit (both groups)

- Before treatment at each visit, the following items are checked:
  - Occurrence of adverse events since the previous visit.
  - Vital signs: sitting blood pressure, pulse rate, body temperature (measured after at least 5 minutes in the sitting position without abrupt postural changes).

---

**4) Assessment visits** (same for Groups I and II – Visits 2, 10, and 11)

(1) All participants who pass screening will visit the outpatient clinic at baseline, at the end of the treatment period (4 weeks after baseline), and 8 weeks after completion of all treatments (12 weeks after baseline) to undergo the following assessments.

(2) Vital signs

(3) Assessment of subjective symptoms and function

- Primary and secondary efficacy outcomes are assessed using questionnaires on pain intensity and function: NRS, ODI, EQ-5D-5L, and RMDQ.

(4) Physical examination

- Lumbar range of motion (ROM):  
Flexion, extension, lateral flexion (right and left), rotation (right and left).

(5) Imaging evaluation

- Standardized lumbar spine AP and lateral standing radiographs (L-spine AP & lateral standing view) are obtained.
- Based on the acquired images, vertebral-level relative angles (flexion, extension, lateral bending, rotation) and Chuna malposition diagnosis results are derived using a DICOM labeling program and compared across time points.

(Note: No separate imaging assessment is performed at Visit 2; the imaging evaluation at Visit 2 is replaced by the screening radiographs obtained at Visit 1.)

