#### (7) Monitoring of adverse events

- In addition to these assessment visits, adverse events are checked frequently during the treatment period through interviews or questioning whenever necessary.

---

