### 5) Early Discontinuation Visit

Participants who have received **at least one session** of the study intervention and then meet the criteria for early termination of the clinical trial will attend an **unscheduled visit 8 weeks after the last treatment session** to undergo an assessment visit. In principle, this assessment should be performed as an in-person visit; however, at the participant's request, items other than physical examination, vital signs, physical function tests, and imaging evaluation may be replaced by **telephone consultation** to the greatest extent possible.

If the clinical trial is terminated early or the participant drops out according to the discontinuation/withdrawal criteria, **no additional follow-up assessments** beyond this early termination visit will be conducted.

---

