## 7) Reporting of adverse events

If a **serious adverse event** or serious adverse treatment reaction occurs during the clinical trial, the principal investigator and sub-investigators must ensure the **safety of the participant** and take prompt and appropriate measures to minimize the adverse event.

- The clinical trial investigator must **immediately report** the event to the principal investigator, who must then report it to the IRB within the timelines specified in the IRB's SOP at each institution.
- The principal investigator and sub-investigators must educate participants (or their guardians) about all potential adverse reactions that may occur after the clinical trial procedures, and instruct them to report all events occurring after the procedures.
- All systemic or laboratory findings that occur after the procedure (type of symptom, time of onset, severity, treatment, medications used, course of the event, causal relationship to the procedure, etc.) must be recorded and stored in the CRF in accordance with Good Clinical Practice.

The principal investigator will describe and evaluate all adverse events that occurred during the clinical trial in the **clinical study report**, and will report serious adverse events to the sponsor and IRB in accordance with applicable regulations.

Serious and **unexpected** adverse treatment reactions must also be reported to the IRB. Additional safety information should be reported periodically until the event is considered resolved (disappearance of the reaction or inability to continue follow-up). Even after completion of the trial, adverse events that occur **within 7 days after the clinical trial procedure** must be reported in accordance with these reporting principles.

The principal investigator will conduct the clinical trial in compliance with all aspects of the **Declaration of Helsinki**.

---

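### After the last session no adverse event enquiry is scheduled for 8 weeks, so detecting short-lived reactions to it depends on self-report and recall

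*Protocol*

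**What the plan says.** Protocol, Section 8, 3) covers Visits 3 to 10, which are the eight sessions. It states: "Before treatment at each visit, the following items are checked". The first item is "Occurrence of adverse events since the previous visit".

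Section 8, 4) sets the assessment visits ("same for Groups I and II – Visits 2, 10, and 11"), so Visit 10 is both the last session and the week-4 assessment. The one later visit is "8 weeks after completion of all treatments (12 weeks after baseline"). Item (7) of the same part adds that "adverse events are checked frequently during the treatment period through interviews or questioning whenever necessary".

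Section 8, 5) gives a participant who stops early an "unscheduled visit 8 weeks after the last treatment session", with no follow-up assessment beyond it.

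Section 14.2 (2) has adverse events confirmed at all visits after randomization and does not say whether this comes before or after treatment. Section 16, 7) tells investigators to instruct participants to report whatever happens after the procedures. It then says, for the time after the trial has been completed, that "adverse events that occur within 7 days after the clinical trial procedure must be reported in accordance with these reporting principles".

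**The concern.** Section 16 lists the expected reactions: mostly pain at the treated site, fatigue, skin irritation and discomfort, with nerve injury and fracture as rare ones. The common ones are short-lived and easily forgotten. For every session but the last, the next twice-weekly visit asks about them while they are fresh. For the last session the same question comes 8 weeks later.

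At stake is the completeness of the adverse event counts, which Section 15, 3) summarizes by group and compares with a Chi-square or Fisher's exact test. Chuna is given only in Group I, so an under-count of Chuna reactions falls in that arm and would tend to narrow the apparent safety difference. The efficacy analysis is not affected.

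**Working it through.** **Inputs (Protocol, Section 8 unless noted).** Two sessions per week for 4 weeks; Visits 3 to 10; checks before treatment, looking back to the previous visit; Visit 11 at 8 weeks after treatment; early discontinuation visit at 8 weeks after the last session; 23 participants per group (Section 6, 3); a 7-day clause (Section 16, 7). The protocol gives no session days, so alternating gaps of 3 and 4 days are assumed.

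**1. The plan's own schedule reproduces.** 2 × 4 = 8 sessions; Visits 3 to 10 are 10 − 3 + 1 = 8 visits; 4 + 8 = 12 weeks.

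**2. Look-back for sessions 1 to 7.** Each is covered by the check before the next session, 3–4 days later and so within 7 days.

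**3. Look-back for session 8.** With the first session on day 0, 1 or 3, the last falls on days 24 to 28. Visit 11 is then 56 days later if counted from the last session, or 84 − 28 = 56 to 84 − 24 = 60 days later if fixed at week 12. In every schedule tried, the number of scheduled contacts in the 7 days after the last session is 0. The 56-day wait is 56/7 = 8 times the 7-day period and 56/4 = 14 to 56/3 ≈ 19 times the look-back for the other sessions.

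**4. Do other provisions close the gap?**
- The additional checks in Section 8, 4) (7) are limited to the treatment period, which session 8 ends, and are made as needed.
- Confirmation at all visits (Section 14.2) adds no visit between Visits 10 and 11.
- If the Visit 10 assessment follows the session (the order is not stated), it catches only immediate reactions.
- The instruction to participants (Section 16, 7) is a real route, but a passive one.

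**5. The 7-day clause for completers.** Session 8 is at about week 4, so 7 days end at about week 5. Completion is at week 12, 12 − 5 = 7 weeks later. A clause that applies after completion therefore adds nothing for completers.

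**6. Share of sessions affected.**

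| | Planned | Last sessions | Share |
|---|---|---|---|
| Chuna (Group I) | 23 × 8 = 184 | 23 | 12.5% |
| Interferential current (both groups) | 46 × 8 = 368 | 46 | 12.5% |

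For an early stopper it is one of the sessions received; after five sessions, for illustration, 1/5 = 20%.

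**7. Weight of one missed case.** With 23 treated in a group, a participant whose only event goes unrecorded lowers that group's percentage with an event by 1/23 ≈ 4.3 points. How many would be missed cannot be derived from the protocol.

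**The case against.** The strongest reply is that the protocol has several routes besides the check before treatment: the as-needed questioning, confirmation at all visits, and the instruction to participants to report. Section 7, 4) also has them consult the team before taking other medication, and Section 11 has rescue medication entered in a diary, so worsening pain may surface that way. The trial is a pilot of 46, its adverse event analysis is largely descriptive, and the gap is one session in eight, scheduled alike in both arms. All of this stands and limits the weight of the point. None of it puts a scheduled enquiry between Visits 10 and 11.

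A reader might infer four stronger things that the document does not support:

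- **That adverse events are asked about only before treatment.** Section 8, 4) (7) and Section 14.2 contradict this.
- **That asking at week 12 breaches the 7-day rule.** The 7 days limit when an event occurs, not when it is asked about. An event on day 3 that is recalled at week 12 is still reportable.
- **That the 7-day clause is empty.** It extends the general duty to record all events and can apply to someone whose participation ends early (Section 9), soon after a session.
- **That reactions are lost for all early stoppers.** Stopping for a serious event or for improvement involves an investigator's or physician's judgement, so a reaction given as the reason will often be known already. The gap matters mainly for those who simply stop attending and for reactions that appear after the last contact.

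**Conclusion.** The point holds as a gap in active follow-up. If the plan is followed exactly, no adverse event enquiry is scheduled for 8 weeks after the last session, or after the last session received before early stopping. Until then detection relies on participants coming forward; after that, on 56-day recall. It touches 1 of 8 planned sessions per completer. The 7-day clause does not help completers as worded, and no scheduled contact supports it after the last session.

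The 56 days and the share of sessions follow from the schedule; the 3–4 day comparison rests on the assumed spacing. The direction of the effect (under-counted Chuna reactions fall in Group I) follows from the design, but its size is unknown. Distortion through unequal early stopping between arms is possible, but nothing in the protocol gives a figure for it. This is an inexpensive improvement to safety ascertainment, not a flaw that threatens the trial's main result.

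**What to change.** - In Section 8, 3) to 5), add one adverse event enquiry about 7 days after each participant's last session, in both groups and including those who stop early. It can be a short telephone call, which the early discontinuation visit already accepts for some items, or an adverse event line in the participant diary already used for rescue medication (Section 11).
- In Section 16, 7), reword the clause so that the 7 days run from the last session received, not from completion of the trial, and refer to this enquiry.

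The cost is protocol wording plus either one diary line or at most 46 short calls (23 × 2) by existing staff. Treatment and the efficacy assessments are unchanged.
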